### 4.3. Intervention: Surgical Procedure and Infection Prevention Measures

All procedures are performed in an electrophysiology ward or an operational theatre with laminar airflow in the ceiling and restricted access during the procedure (no OR traffic). 

➢
**Pre-procedural (intervention):**

The participant’s torso, legs, and arms should be fixed to the table. If necessary, chest hair should be clipped. The use of an external defibrillator and the recording of an intraprocedural electrocardiogram represent the standard of care. Intravenous antibiotic prophylaxis with a cephalosporin within 60 min or vancomycin within 120 min is mandatory. Antiseptic skin preparation is performed with a polyvinylpyrrolidone-iodine (PVP-I) or chlorhexidine (CHX) wash according to the centre’s standard of care, including the chest wall, both shoulders, the upper arms, and the neck. The use of polypropylene adhesive drapes and gowns and double gloving are encouraged in the contributing centres. Patients are either operated on under conscious sedation with intravenous/oral benzodiazepine or no sedation, except in cases of the implantation of a subcutaneous defibrillator (S-ICD), where general anaesthesia may be performed.

➢
**Procedure (intervention) with adjunct TP:**

For de novo, upgrade/downgrade revision, early revision, or generator exchange and further clarification, please refer to the SOP CIED placement or SOP CIED revision in the Supplementary Materials section of this manuscript and on www.etpr.eu.

*De novo placement:* After the subcutaneous administration of local anaesthesia, the skin is incised. The generator pocket is prepared. After the placement of the sheath, the pocket is rinsed with TP. The first lead is wiped down and the suture sleeve mobilised with a TP-soaked swab. After placement, the fixation sleeve surrounding the lead is moved to its final position by gripping it with a TP-soaked swab. When sutured to the tissue, the lead, sleeve, and suture are irrigated with 5–10 cc of TP. Subsequent lead placements are carried out accordingly. Before connecting the leads to the generator box, the generator is wiped down with or fully immerged in TP. Both the lead and the generator are gripped with a TP-soaked swab when plugging the lead into the port. The torque wrench is immerged in TP before engaging with the set screws. Once all the hardware is in its final position, the pocket is rinsed with the remainders of the TP. The wound is closed. 

For de novo, upgrade/downgrade revision, early revision, or generator exchange of S-ICDs and further clarification, please refer to the SOP S-ICD in the Supplementary Materials section of this manuscript and on www.etpr.eu.

*Generator exchange, CIED upgrade or downgrade, any revision:* The skin of the pocket is incised cranially (avoiding skin incision “covering” the CIED). After gaining access to the generator pocket and before mobilizing the indwelling generator, the pocket is irrigated with TP (a substantial percentage of the indwelling generators may be contaminated with dormant bacteria [30]), which helps with mobilisation. The old generator is extracted from the pocket. The generator is disconnected. In the cases of substitution and upgrade revision (and a new lead in the case of an upgrade revision), the new generator is washed and wrapped in a TP-soaked swab. Then, the leads (after placement in the event of an upgrade revision) are subsequently connected to the new generator using a TP-soaked swab to grip the leads to plug them into the ports. Before engaging with the seals covering the set screws, the new torque wrench is immerged in TP to prevent contamination. Before positioning the new CIED generator, the empty fibro-collagenous pocket with the old leads in place is repeatedly rinsed with TP (5 cc each). After the final placement of the generator, all hardware is irrigated with TP prior to wound closure. “Breaking” the pocket (the induction of bleeding inside the pocket is hypothesized to trigger a humoral immune response to the possible contamination of the pocket; however, this brings with it the risk of inducing a hematoma) is at the operator’s discretion but is not recommended [1].

Other measures to prevent CIED infection, like additional pocket irrigation with antibiotics or antiseptics or the use of the antibiotic mesh envelope, are discouraged during the procedure in the contributing centres (when TP is used, no oxygenising agent like iodine or chlorhexidine should be used in the pocket or on the CIED).

➢
**Postprocedural:**

The surgical site is cleaned with PVP-I- or CHX-soaked swabs after skin closure. A sterile surgical dressing with an additional pressure dressing (including a sandbag or special bandage where available) is applied. Before the patient is discharged from the hospital, the wound is inspected and the CIED parameters are tested. Participants are trained to observe the surgical site and instructed not to take a full body bath for the following 10 days and not to swim, carry heavy loads, or exercise for the following six weeks. When showering, participants are trained not to moisten the surgical site and to use a waterproof wound dressing, which is given to them upon discharge from the hospital.

### 4.4. Termination

Participants can terminate their participation in the study at any time without providing reasons. The participants may freely withdraw consent at any time without creating any disadvantages for patient-centered care.

Some potential reasons for the premature termination of the study are the identification of unacceptable risks, or incidents leading to an unacceptable benefit–risk assessment.

### 4.5. Data

The registry allows for a full survey. The data model is based on the following data sources: primary center-based data collection e.g., on specific indication criteria and on the indication of the product under investigation (comorbidities). Indication criteria comprise patient-related risk factors (<65 years, male gender, renal impairment, COPD, heart failure, chronic skin disease, malignancy, immunosuppression, oral anticoagulation, dual platelet inhibition, diabetes mellitus, hematoma formation, and previous implant infection) and procedure-related risk factors (procedure duration longer than 59 min, inexperienced operator, revision, generator substitution, abandoned lead, more than two leads placed, temporary pacing, and bulkier/heavier devices: S-ICD, ICD, CRT), which are recorded. 

## 5. Endpoints

The primary endpoint is major CIED infection during follow-up.

Major CIED infections are defined in the novel CIED infection criteria [1], resulting in [8]: CIED system removal;an invasive CIED procedure (pocket revision without removal);surgical site infection resulting in pocket revision or CIED extraction after systemic antibiotic therapy;chronic antibiotic therapy due to a major CIED infection without an invasive procedure;death.

Secondary endpoints include all-cause mortality, major CIED pocket infection, minor CIED infection, TP-related adverse device effects (ADE), CIED-procedure-related or CIED-hardware-related adverse events (e.g., pain, arrhythmia, hematoma formation that is resolved, pneumothorax that is resolved), and complications (e.g., hematoma formation requiring revision, pericardial effusion requiring drainage, pneumothorax requiring chest tube, events requiring early pocket revision) during all follow-up periods.

### 5.1. Endpoint Assesment

General: Participants will be trained to be aware of the clinical criteria as defined in Section 4. Participants will be told to call whenever the slightest signs of the defined criteria are noted or in any case of unusual or suspect indisposition. If the call indicates CIED infection, adverse events, or incidents, the participant calling will be examined in the ward by a cardiologist or cardiac surgeon with expertise in rhythm surgery. A decision on the presence of a CIED infection, adverse event, or other incident will be made according to the examination results and the clinical criteria defined.

If an infection is suspected, the initial tests include (but are not limited to) an examination (inspection, temperature, questioning), trans-thoracic echocardiography (TTE), trans-oesophageal echocardiography (TEE/TOE), a complete blood count, and repeat blood cultures (at least three sets taken from different sites; blood sampling from any central venous line is prohibited). In case of hardware exposure, re-intervention, or extraction, swabs and tissue samples of the pocket interior and hardware are sent to the local microbiology lab for analysis.

### 5.2. Follow-Up Schedule

Table 1 contains the follow-up schedule after the procedure.

## 6. Statistical Analysis

The ETPR is designed for comparisons between the intervention with TP and historical controls, with a two-sided confidence level of 0.95. The primary estimand is the rate of patients who develop a CIED infection after a CIED procedure with adjunct TP before a repeat procedure (i.e., system modification) on that CIED is performed or the patient succumbs. This rate of infection is needed to evaluate the intervention with TP during CIED placement procedures. Exact binomial statistics will be used for CIED infection rates at 3 and at 12 months, estimated as the number of procedures followed by a CIED infection relative to the number of registered procedures with at least the respective follow-up times or an event within the specified time periods. For the first sensitivity estimand, the intercurrent events (Table 2) of generator replacement, system change, revision (i.e., any procedure that touches the CIED within the follow-up period), and death are considered to be competing risks in the estimation of the cumulative incidence curve. Event times end at these events, as these events can trigger CIED infections, but sub-distribution hazards are used to calculate the cumulative incidence function. This leads to fewer upward-biased estimates than when considering these intercurrent events as censoring the event time. Censoring is restricted to failure to follow-up (i.e., death, discontinuation) and the end of observation (i.e., system modification). Other intercurrent events, such as the intravenous administration of antibiotics (e.g., in the treatment of pneumonia), will not be considered, as in the published intention-to-treat data. Their sum is expected to be independent of TP use. This decision is taken to avoid estimates that are too low for the evaluation of the intervention.

Another objective is to gather planning data for future studies. In randomised controlled trials (RCT), the primary estimand is the cause-specific hazard ratio. This translates into censoring at the occurrence of competing risks. The second sensitivity estimand of the ETPR is the rate of major CIED infections per time survived without competing risks. 

The confidence level will not be adjusted for multiple checks, as all analyses will be performed, and conclusions will be based on the latest results of the interim analyses or final results only. Times to major CIED infection or to death will be analysed using Kaplan–Meyer curves and cause-specific hazard ratios for the numbers of risk factors related to the patient, the CIED, or the procedure. ADE and complications will be analysed similarly using logistic regression.

The secondary estimand is all-cause mortality after CIED procedures using TP between procedures accessing the pocket. Intercurrent events are handled similarly (see Table S1 in the online supplement).

To facilitate causal inference in future research, the known risk factors for major CIED infection are reported. Their distribution should enable the calculation of propensity scores or more general balancing weights [31]. Such analyses would consider the randomness of historic controls instead of using historic results as performance goals.

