### 4.2. Inclusion/Exclusion

The present prospective observational study includes all consecutive patients with adjunct TP use during CIED placement. This may be in unselected patients (centres that use TP in all patients) or in patients with an anticipated risk for CIED infection according to the results of the PADIT calculator [7] (centres that use TP in high-risk patients only). CIED placement procedures include any invasive CIED procedure (i.e., revision, upgrade/downgrade with or without lead placement, or generator substitution) with adjunct TP treatment of all the CIED hardware before, during, and after placement in patients eligible to undergo a CIED placement procedure receiving any CIED (including and not limited to PPM, ICD, CRT-P, CRT-D, S-ICD, and CCM).

Every procedure with TP enters the final analysis. Standard of care comprises inspection, electrocardiogram, laboratory testing, and cardiac ultrasound for placement and a CIED interrogation in the event of generator replacement, upgrade or downgrade revision, and early revision. Additional medical examinations and diagnostics are performed according to medical needs (i.e., computed tomography angiography, vascular ultrasound, Holter electrocardiogram, coronary computed tomography, cardiac magnetic resonance imaging).

An inability to sign the patient informed consent will lead to the patient’s exclusion.

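### The TP infection rate stops at a repeat procedure, but the protocol does not show that the published rates used as fixed goals stop there too

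*Protocol article*

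**What the plan says.** Section 6 states that the registry is designed for comparison with historical controls, "with a two-sided confidence level of 0.95". Three estimands of the infection rate are planned, and all stop at re-intervention in some form:

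- **Primary:** infection "before a repeat procedure (i.e., system modification) on that CIED is performed or the patient succumbs". It is estimated by exact binomial methods as infected procedures "relative to the number of registered procedures with at least the respective follow-up times or an event within the specified time periods".
- **First sensitivity:** generator replacement, system change, "revision (i.e., any procedure that touches the CIED within the follow-up period), and death are considered to be competing risks". The reason given is: "Event times end at these events, as these events can trigger CIED infections". Table 2 lists the bias so prevented as upward for box exchange, system modification and other pocket interventions.
- **Second sensitivity:** infections per time survived free of competing risks.

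Section 6 also lists system modification as an end of observation. Table 3 then sets the TP rate against literature rates treated as fixed external goals, among them 1.2% (WRAP-IT control) and 1.03% (PADIT) at 12 months. The unit of analysis is the procedure. Revisions and generator exchanges are eligible, and Section 4.2 says: "Every procedure with TP enters the final analysis".

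**The concern.** A comparison of two proportions is fair only if both count infections over the same period. On the TP side, the period closes when the pocket is re-opened, because the plan regards re-opening as a source of infection. On the goal side, the article gives no counting rule for any row of Table 3. If a published rate includes infections that followed a re-intervention, the goal contains a component that the TP rate leaves out.

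The loss is not total. A re-intervention done with TP and registered beforehand is a new row, and a later infection counts there. What is lost is infection after a re-intervention that was done without TP, not registered, or done elsewhere. Section 2 follows only procedures registered beforehand, Table 2 gives no follow-up when another or no disinfectant is used, and Section 4.2 allows centres to use TP in high-risk patients only. Such losses are therefore possible. No planned estimate follows the index procedure through a re-intervention, so a reader could not tell how much of an apparent advantage comes from the counting rule.

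**Working it through.** **Inputs from the protocol.** Goal p0 = 1.03% (PADIT, 12 months), expected TP rate p1 = 0.5%, N = 2300 for the exact test with 80% power, N = 681 for the confidence-interval column (Table 3), two-sided 95% level (Section 6).

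**Assumed inputs.** r is the share of index procedures re-intervened within 12 months without a prior infection, taken as 3-8%. q is the share of these with a major infection afterwards, within 12 months of the index procedure, taken as 1.5-4%. The protocol gives neither. The Introduction's figures of around 10% complications and 1.2-4.2% infections are related but are not r or q.

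**Step 1: reproduce the plan's figures.**
- Confidence-interval column: 1.96² × 0.005 × 0.995 / (0.0103 − 0.005)² = 680.4, stated as 681.
- Exact test, lower tail 0.025 (two-sided 5%): at N = 2300 superiority is declared with 14 or fewer infections. P(X ≤ 14) is 2.2% at a true rate of 1.03% and 81.6% at 0.5%. This agrees with the stated 80% power.

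**Step 2: the counted TP rate if TP has no effect and the goal includes later infections.** Infections before re-intervention are p0 − rq. On the stated denominator, a cut-short procedure has neither full follow-up nor an event and drops out, leaving 1 − r. With no re-entry:

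counted rate = (p0 − rq)/(1 − r), so shortfall = p0 − counted rate = r(q − p0)/(1 − r).

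**Step 3: the false-claim probability.** This is P(X ≤ 14) at N = 2300 for the counted rate.

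| r | q | Counted rate | Shortfall (points) | False-claim probability |
|---|---|---|---|---|
| – | – | 1.03% | 0 | 2.2% |
| 3% | 1.5% | (1.03 − 0.045)/0.97 = 1.015% | 0.015 | 2.6% |
| 5% | 2% | (1.03 − 0.10)/0.95 = 0.979% | 0.051 | 3.8% |
| 8% | 4% | (1.03 − 0.32)/0.92 = 0.772% | 0.258 | 22% |

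The planned difference is 1.03 − 0.50 = 0.53 points, so the shortfall is about 3% of it at the low end and about half at the extreme.

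**Step 4: re-entry.** If a fraction f of the re-interventions is registered with TP and each later infection counts on the new row, the counted rate is (p0 − rq + f·rq)/(1 − r + f·r). With f = 1 it returns to p0, and the false-claim probability to 2.2%. With f = 0.5 at r = 8%, q = 4%, it is (1.03 − 0.16)/0.96 = 0.906%, and the probability is 7.5%.

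**The case against.** The case for the plan is substantial, and most of it stands.

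- **Intention-to-treat wording.** A reader might infer that the plan calls its comparators intention-to-treat and then departs from that for re-interventions. The phrase "will not be considered, as in the published intention-to-treat data" explains only why other intercurrent events, such as intravenous antibiotics, are ignored. The stated aim of avoiding estimates that are too low belongs to the same sentences. Neither shows that the goals count infections after re-intervention, so no self-contradiction is established. Table 3 also includes a registry and insurance data, which the text does not call intention-to-treat.
- **Trials censor too.** Section 6 says that the primary estimand in randomised trials is a cause-specific hazard ratio, and adds: "This translates into censoring at the occurrence of competing risks". This weakens any claim that no planned estimate matches the comparators. It does not settle the point, because the sentence concerns hazard ratios for planning future trials, whereas Table 3 compares proportions.
- **Re-entry.** It would be wrong to say that infections after re-intervention never count against TP. With full re-entry the effect vanishes (Step 4).
- **Denominator.** Taking the shortfall as r × q (0.045-0.32 points) keeps cut-short procedures in the denominator. The stated denominator does not support that, and the smaller formula in Step 2 applies.
- **Scope.** Stopping at any procedure that touches the device is the wording of the first sensitivity estimand. The primary estimand glosses the repeat procedure as system modification.
- **An explained choice.** Ending an index procedure's risk period when the pocket is re-opened is legitimate for a TP-specific rate. The Sample Size section admits that the goals are heterogeneous, and Section 6 foresees weighted comparisons in future research.

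What remains is that the stopping rule is documented on one side of the planned comparison only.

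**Conclusion.** The point holds as a possible bias towards TP, not as a demonstrated one. It depends on a goal counting infections after re-intervention, which the documents neither state nor exclude, and on some re-interventions falling outside the registered TP procedures.

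Under the assumed r and q, with no re-entry and cut-short procedures out of the denominator, the effect runs from negligible (0.015 points, false-claim probability 2.6%) through modest (0.051 points, 3.8%) to serious (0.26 points, about 22%), against 2.2% with no mismatch. Partial re-entry pulls every figure down. A reader might take the top of this range as the expected bias. The documents do not support that, because r, q and the re-entry fraction are all unknown. The point is worth settling because the comparison with goals is what the registry is designed for and the remedy is cheap.

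**What to change.** 1. Keep the present primary estimand as the TP-specific rate.
2. For comparisons with published goals, add a treatment-policy sensitivity rate: any major CIED infection within 12 months of the index procedure counts, whether or not the pocket was re-opened in between. Count each infection once per patient and device, so that an infection after a registered TP re-intervention is not counted on both rows.
3. State that the index procedure's scheduled visits continue to be recorded after a re-intervention, including one done elsewhere or without TP. Table 1 schedules visits to 36 months, but Section 6 treats system modification as an end of observation. If recording stops there, the rate cannot be recovered later.
4. For each goal in Table 3, state whether infections after re-intervention are included, or that the source does not say.

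The cost is a little more analysis, continued recording at visits already scheduled, and a slightly less favourable rate in the comparison.

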## 2. Clinical Evaluation Plan

The ETPR is part of an investigator-initiated clinical development plan. The objective of this clinical development plan is to establish adjunct TP use in CIED procedures. The roadmap to that goal lists several studies to address the different research questions that will have to be answered. These follow the phases set out in the IDEAL framework [13]. 

Idea (IDEAL Stage 1): Taurolidine use is common in locking solutions and recommended in the current guidelines and consensus documents [14,15,16,17,18,19]. Taurolidine solutions are used during lung transplantations [20]. Taurolidine was researched for adjunct use during dental implantation, with a focus on how it affects the buccal microbiome [21,22]. It has shown good results when used during spinal fusion surgery [23]. Taurolidine has been used in different galenic formulations to treat infections in difficult settings [24]. Life-threatening ventricular assist device driveline infections and localised major CIED infections (pocket) were salvaged via debridement using adjunct taurolidine irrigation as a method of last resort [25,26,27,28,29]. 

Development (IDEAL Stage 2a): The physicians involved developed the routine use of adjunct TP during CIED placement and elaborated the standard operating procedure outlined below and on the ETPR website (www.etpr.eu; accessed on 1 June 2023). One manufacturer conducted the preclinical testing and obtained the “Conformité Européenne” for a taurolidine solution: TauroPace™. The investigator-initiated ETPR recording adjunct TP use during CIED procedures follows consecutive cases from multiple centres in a prospective manner [Figure 1]. As the estimation of the infection rate needs to be defensible, only interventions registered prior to the procedure will be followed-up. As the rate of CIED infections is expected to be very low, this registry is a multicentric, international endeavour that will run for several years (ETPR plans to include 2300 procedures and to run until 2030; this depends on the number of centres willing to participate and the annual rate of CIED procedures with adjunct TP use in these centres). Four reports are planned. Analyses will inform the case number calculations for the future studies outlined in Stage 3. The positive reporting of safety will improve the manufacturer’s post-marketing surveillance of safety issues that might otherwise be reported by employing physicians only in clinically relevant cases.

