### Sample Size

The performance goals for the rate of major CIED infections vary according to country, evidence level, CIED type, and patient selection. They are expected to be higher in a revision procedure involving a complex CIED in high-risk patients than for de novo implants in otherwise healthy patients within a well-maintained setting. Additionally, the novel criteria for major CIED infection have evolved [1]. Accordingly, the published 12-month rates range from 0.7% to 4.2% (Table 3). The three-month rates are available from WRAP-IT and the Danish device registry, with values of 0.8% and 1.0% in controls, respectively [32]. For future studies researching TP use, we expect to plan for a 12-month rate of 0.5%. If its ratio to the three-month rate is 0.8/1.2, as in the WRAP-IT controls [8], then we assume a three-month rate of 0.33%.

For an approximate 95% confidence interval, to exclude a risk difference of 0.8% − 0.33% = 0.47%, when the true event rate is 0.33%, the sample size needs to exceed 572. 

For an exact 5% binomial test to have a power of 80% in detecting the difference between the hypothetical rate of 1% (0.8%) and the true rate of 0.33%, the sample size needs to be 1140 (2000).

Assuming a major CIED infection rate in the registry of 0.5% at 12 months and 0.33% at 3 months, a comparison with the performance criteria from the literature would require the sample sizes shown in Table 3.

We therefore plan to publish the ETPR results after the twelve-month follow up of 400, 900, 1420, and 2300 procedures. For the long-term evaluation, a report after the follow-up period of 36 months is planned for all procedures enrolled.

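### The primary 3- and 12-month infection rates count a procedure with incomplete follow-up only if it had an event, which biases the reported rate modestly upward

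*Protocol article*

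**What the plan says.** All references are to the protocol article.

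- **Estimand (Section 6).** The primary quantity is the rate of patients who develop a CIED infection "before a repeat procedure (i.e., system modification) on that CIED is performed or the patient succumbs".
- **Estimator (Section 6).** Exact binomial statistics are applied. The numerator counts infected procedures, and the denominator is worded as follows: "relative to the number of registered procedures with at least the respective follow-up times or an event within the specified time periods".
- **Ends of observation (Section 6).** "Censoring is restricted to failure to follow-up (i.e., death, discontinuation) and the end of observation (i.e., system modification". Death and re-procedure thus end follow-up, as discontinuation does.
- **Competing risks (Section 6, Table 2).** "For the first sensitivity estimand, the intercurrent events (Table 2) of generator replacement, system change, revision", together with death, are treated as competing risks. Table 2 gives the bias prevented by this handling as upward. It is assigned to the first sensitivity estimand, not to the primary rate.
- **Analysis set (Section 4.2).** "Every procedure with TP enters the final analysis".
- **Reports (Sample Size).** The plan is to "publish the ETPR results after the twelve-month follow up of 400, 900, 1420, and 2300 procedures"; Section 2 adds that the "ETPR plans to include 2300 procedures and to run until 2030".

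**The concern.** Under the estimand, a patient who dies or is re-operated at month 5 without infection is a known non-event and belongs in the denominator. The estimator requires the full follow-up time or an event. If *event* means infection, that patient is removed, while a patient infected at month 4 who dies at month 5 stays. Membership of the denominator then depends on the outcome, and the estimator no longer targets the stated estimand.

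The same selection can act through loss to follow-up. It can also act through recent procedures, if a report's data cut includes any that have not yet reached 12 months.

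At stake are the headline rate, which is compared with fixed historical goals of about 1%, and the power of those comparisons. When the planned rate is 0.5%, small absolute shifts matter.

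**Working it through.** **Inputs from the article.** Planned rates: 0.5% at 12 months and 0.33% at 3 months. Performance goals at 12 months: 1.2% (WRAP-IT controls) and 1.03% (PADIT). Report sizes include 400, 1420 and 2300. The level is 5%, "with a two-sided confidence level of 0.95".

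**Assumed inputs.** The share d of procedures ending before 12 months is not given; 5%, 10% and 20% are used. Accrual is not given; 10 to 30 procedures per month are used.

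**Step 1: the plan's own figures.**
- Confidence-interval size: n = 1.96² × p₁(1−p₁)/(p₀−p₁)². With p₁ = 0.33% and p₀ = 0.8% this gives 572, as stated.
- Exact test, lower tail 0.025, 1.2% versus 0.5%: at n = 1420, success means at most 9 infections, with power 82.1%. This is the first n to reach 80%, as stated.
- Exact test, 1.03% versus 0.5%, n = 2300: success means at most 14 infections, with size 0.0223 and power 81.6%.

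**Step 2: direction.** Let N be all procedures, C those with complete follow-up, I all observed infections and I_inc the infections among incomplete procedures. On the infection-only reading the estimator is I/(C + I_inc). Since C + I_inc ≤ N, it can never fall below I/N.

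**Step 3: death and re-procedure.** Take 5 infections in 1000 procedures, so I/N = 0.500%, and drop the infection-free procedures that end early.

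| Dropped | Reported rate | Relative to 0.500% |
|---|---|---|
| 50 | 5/950 = 0.526% | +5% |
| 100 | 5/900 = 0.556% | +11% |
| 200 | 5/800 = 0.625% | +25% |

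The factor is 1/(1−d).

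**Step 4: independent loss to follow-up.** Infections after loss go unseen, so the effect is smaller. Take losses as uniform over 12 months and cumulative infection as linear between 0, 0.33% at month 3 and 0.50% at month 12. The average cumulative incidence at loss is (3 × 0.165% + 9 × 0.415%)/12 = 0.3525%. At d = 10%, observed infections per procedure are 0.9 × 0.5% + 0.1 × 0.3525% = 0.485%. The denominator is 0.9 + 0.1 × 0.003525 = 0.90035, so the reported rate is 0.539%. At 5% and 20% it is 0.518% and 0.588%.

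**Step 5: power against 1.03% with 2300 evaluable procedures.** Success still means at most 14 infections.

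| d | Expected reported rate | Power |
|---|---|---|
| 0 | 0.500% | 81.6% |
| 5% | 0.526% | 76.3% |
| 10% | 0.556% | 69.8% |
| 20% | 0.625% | 53.1% |

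With independent loss only, at d = 10% (0.539%), power is about 74%.

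**Step 6: immature procedures in an interim cut.** With 20 procedures per month, the last 12 months contribute 12 × 20 × 0.003525 = 0.85 expected infections and, apart from those, no denominator. The 400-procedure report then shows (2 + 0.85)/(400 + 0.85) = 0.71% instead of 0.50%. At 10 and 30 per month it is 0.61% and 0.81%.

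**The case against.** **The word *event* is not defined.** The numerator speaks of CIED infection and the denominator of an event, and the following sentences use *events* for death and re-procedure. If the denominator covers those too, uninfected deaths and re-operations stay in, and the conflict with the estimand largely goes. This also fits the Section 4.2 statement on the analysis set better. The objection stands in part. The infection-only reading is more natural, because the sentence concerns infections within set periods. On either reading, lost and immature procedures remain selected on outcome.

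**The right analysis is already planned.** The first sensitivity estimand treats death and re-procedure as competing risks, and the second gives a separate quantity for trial planning. This stands, so a reader should not infer that the registry cannot inform a later trial. The sensitivity result does not, however, correct the primary number.

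**The bias is conservative.** This stands. An overstated rate makes superiority over a fixed goal harder to show.

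**Stronger readings that a reader might infer:**
- *That every report is overstated by the enrolment tail.* The reports are tied to twelve-month follow-up of a given number of procedures, which can be read as those procedures only. If enrolment closes at 2300, the final report need have no tail. Step 6 is conditional.
- *That power falls from 82% to 63% at 10% attrition.* This takes 2300 as registered, leaving 2070. The Sample Size section counts procedures with twelve-month follow-up, and at n = 2070 an unbiased 0.5% already gives only 76%, so part of the drop is sample size.
- *That the rate cannot be compared with the performance goals at all.* This depends on how the historical rates were computed, which the article does not show.

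**Conclusion.** The point holds in limited form. As worded, the primary denominator depends on the outcome. On the infection-only reading it contradicts the estimand in the same section, and the upward direction for deaths and re-procedures follows from arithmetic alone. For loss to follow-up, the upward direction assumes that loss is independent of infection; infections missed among lost patients could offset it.

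The size is modest and rests on an attrition share that the article does not give. At 5% to 20%, the rate is overstated by roughly 5% to 25% in relative terms, and power against 1.03% drops below the planned 80% throughout that range. An interim tail of immature procedures could matter more at the 400-procedure report, but only if the data cut includes them.

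False claims of success are not made more likely. This should be fixed, because it changes the primary number and is cheap to repair, but it does not undermine the registry.

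**What to change.** Rewrite the estimator paragraph in Section 6.

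1. Restrict each report to procedures registered at least 3 (or 12) months before the data cut.
2. State that death or a repeat procedure without prior infection is a non-event for the primary rate, and define *event*.
3. Make the already planned competing-risk cumulative incidence (Aalen–Johansen), with its confidence interval, the primary 3- and 12-month estimate. Censor only true loss to follow-up and administrative end of observation.
4. If the exact binomial is kept, apply it to the same entry-date cohort with deaths and repeat procedures as non-events. Exclude patients truly lost before the time point whatever their infection status, or show bounds for them. Counting them as uninfected would bias the rate downward: 0.485% against a true 0.50% at 10% loss, on the assumptions of Step 4.

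The cost is one paragraph of wording, with no new data and no extra patients. The small downside is that the cumulative-incidence interval is not an exact binomial interval.
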